### 2.5. Procedure

#### 2.5.1. Intervention

##### Digital Health Services Group (DHSG)

Children randomized to the DHSG will engage in a home-based hybrid (synchronous and asynchronous), remotely administered exercise program and ACTs for 12 weeks. The prescribed weekly regimen will consist of 50 min remote sessions: two synchronous, supervised sessions conducted via the Vsee platform, and a minimum of one asynchronous, unsupervised session. Children will be encouraged to maintain daily adherence to the exercise protocol.

Secure access to the VSee platform will be granted through a unique identification code assigned to each child. Parents/guardians will receive written and verbal instructions regarding the Vsee platform setup, the equipment’s proper use, and safety procedures, including “actions in an emergency” in case of adverse events or technical issues. Adverse events are defined as unintended injuries or clinical incidents resulting from study participation. These include complications such as paroxysmal cough, severe dyspnea, oxygen desaturation (4% drop in SpO_2_), musculoskeletal injury, or loss of balance. To ensure safety in any adverse event (e.g., falls, injury, etc.), at least one parent or guardian will be required to be present in person with the child during sessions. Additionally, written first-aid advice will be given. All adverse events will be recorded during the synchronous videoconferencing sessions. The physiotherapist will document the nature, severity, and duration of each event in a standardized log.

Children will perform ACTs (including individualized teaching and review of postural drainage, percussion, vibration, ACT devices, huffing, coughing), diaphragmatic breathing, and blowing games to enhance mucus expectoration. Both children and parents will be taught how to perform these techniques. During the synchronous, supervised videoconference sessions, the DHSG will be monitored/supervised by the pediatric respiratory physiotherapist for the proper performance of ACTs (device or non-device). All children will perform ACTs once a day for ten minutes. In case of mucus excess, they will be suggested to increase the performance to twice a day. ACTs will be chosen based on children’s ability to use/cooperate and preferences.

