##### Compliance with the Airway Clearance Techniques and Exercise Program

Compliance with the ACTs will be recorded using a detailed diary that includes weekly symptoms, type, frequency, and duration of ACTs performed. For both groups, compliance will be assessed twice a month, following the completion of this diary. The DHSG will complete the diary through the website, while the CG will complete it in a paper version via a phone call from a physiotherapist. Furthermore, the DHSG’s exercise program compliance will be assessed every second online session through a Microsoft Form diary. Documentation of the percentage of completed synchronous videoconferencing sessions will also be performed.

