### 2.9. Sample Size Calculation

Due to the lack of pilot data for this specific population, the effect size was estimated a priori. We targeted a moderate effect size (f = 0.25), assuming that this represents a clinically significant improvement in exercise capacity for children with CSLDs. The required sample size was calculated with G*Power version 3.1.9.4 (G*Power, University of Düsseldorf, Düsseldorf, Germany). The “F-test” (ANOVA: repeated measures, within-between interaction) and the detection of a moderate effect size f = 0.25 (alpha level = 0.05, power = 80%) showed that a total of twenty-eight children are required. Assuming a dropout rate of 10%, the total sample size is estimated at thirty-two children, with sixteen in each group.

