### 2.10. Statistical Analysis

Statistical analysis will be performed using IBM SPSS—Mac, Version 31.0 (IBM Corporation, Armonk, NY, USA). The normal distribution of the variables will be demonstrated using the “Shapiro–Wilk” test. The analysis will be performed using an intention-to-treat (ITT) approach, and all the randomized participants will be included (including those who may discontinue the study or be noncompliant with the assigned therapy). Reasons for discontinuing the study will be recorded. Missing data will be handled through a two-stage approach. Initially, we will re-contact (recall) all participants who have incomplete data. For the remaining missing values, multiple imputation (MI) will be employed [42]. Parametric and non-parametric analyses will be performed, based on the normal distribution of the variables. A separate 2 × 3 mixed-model analysis of variance (ANOVA) will be used to examine the effects of the intervention on the primary and secondary outcomes. For the group × time interaction in the ANOVAs, the factors that will be analyzed are group (DHSG and CG) and time (baseline, end of treatment, and follow-up). For this test, a partial eta-squared (η^2^) of 0.01–0.059 represents a small effect, a value of 0.06–0.139 represents a medium effect, and a value >0.14 represents a large effect. Differences between measurements will be analyzed using Bonferroni correction. A *p*-value < 0.05 will be considered statistically significant for all the analyses.

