**Primary outcomes**					
Exercise capacity (MSWT)			X	X	X
Compliance (ACTs and exercise)			X	X	X

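### Diary-based compliance, part of a listed primary outcome, falls under the general multiple-imputation rule, which would tend to overstate adherence where entries stop because a child stops taking part

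*Protocol article*

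**What the plan says.** Table 1 of the protocol article lists "Compliance (ACTs and exercise" (the bracket closes there) among the primary outcomes, and the compliance paragraph stands under the primary-outcome heading in 2.8.1. That paragraph describes three records:

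- **Airway clearance diary, both groups, assessed twice a month.** The intervention group completes it on the website. The control group completes it on paper during a physiotherapist's phone call.
- **Exercise diary, intervention group only:** "exercise program compliance will be assessed every second online session through a Microsoft Form diary".
- **Session record, intervention group only:** "Documentation of the percentage of completed synchronous videoconferencing sessions will also be performed".

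The intervention section sets the weekly schedule at "two synchronous, supervised sessions conducted via the Vsee platform, and a minimum of one asynchronous, unsupervised session", for 12 weeks.

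Section 2.10 analyses all randomized children, "including those who may discontinue the study or be noncompliant with the assigned therapy". For gaps it says: "Initially, we will re-contact (recall) all participants who have incomplete data". It continues: "For the remaining missing values, multiple imputation (MI) will be employed". It makes no exception for compliance. It does not say that an empty diary or a missed session counts as not done, and 2.8.1 does not say which of the two exercise records is the compliance measure.

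**The concern.** For a walking test, a missing value hides a measurement that could have been taken. For adherence, the gap can itself be the result: a child who gives up the program may also stop filling in the diary. Standard multiple imputation assumes that, given the variables in the model, the missing values resemble the observed ones. Applied to these gaps, it would fill the weeks after stopping largely from children who kept reporting. Re-contact helps, but families who have disengaged are likely to be the hardest to reach.

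At stake is how well the program appears to have been followed. An outcome listed as primary could look better than it was, and most so where adherence was worst.

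**Working it through.** **Plan's own figure.** The article gives no expected compliance, so there is none to reproduce. The only related number is in section 2.9: "Assuming a dropout rate of 10" per cent. For 16 children per group that is 0.10 × 16 = 1.6, or about 1 to 2 children. It is trial dropout, not a forecast of empty diaries, and serves here only to choose a plausible count.

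**Inputs from the article**

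- Scheduled video sessions: 2 per week × 12 weeks = 24.
- Exercise diary points, one per two online sessions: 24 / 2 = 12.
- Asynchronous sessions: at least 1 × 12 = 12.
- Children in the intervention group: 16.

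**What each record shows for a child who attends everything and then stops after *s* sessions**

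| Stops after | Session record (*s*/24) | Diary points already made (*s*/2) | Diary points that may be empty |
|---|---|---|---|
| 6 | 25% | 3 | 9 |
| 12 | 50% | 6 | 6 |
| 18 | 75% | 9 | 3 |

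The session record stays observed and falls as it should. Only the diary can have a gap.

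**Size of the diary bias.** Assumptions, none of them in the article: adherence *p* = 80% while taking part; adherence *q* after stopping; entries cease on stopping; imputation ignores attendance and so fills gaps at *p*. With *d* children stopping:

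- Imputed group mean = *p* = 80%.
- True group mean = [(16 − *d*) × *p* + *d* × ((*s*/24) × *p* + (1 − *s*/24) × *q*)] / 16.
- Overstatement = (*d*/16) × (1 − *s*/24) × (*p* − *q*).

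With *d* = 2, *s* = 6 and *q* = 0, the true mean is (14 × 0.80 + 2 × 0.25 × 0.80) / 16 = 11.6 / 16 = 72.5%, against 80% imputed: 7.5 points too high. With *s* = 12 it is 12.0 / 16 = 75% (5 points), and with *s* = 18 it is 12.4 / 16 = 77.5% (2.5 points).

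Overstatement in percentage points, over the range of assumptions:

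| Children stopping (of 16) | *q* | Stop after 6 | Stop after 12 | Stop after 18 |
|---|---|---|---|---|
| 1 | 0% | 3.75 | 2.5 | 1.25 |
| 2 | 0% | 7.5 | 5 | 2.5 |
| 4 | 0% | 15 | 10 | 5 |
| 2 | 40% | 3.75 | 2.5 | 1.25 |

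The last row shows that the bias halves if children keep up half their earlier adherence, since (0.80 − 0.40) / 0.80 = 0.5.

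**The case against.** The strongest reply is that a child who stops is not invisible. The percentage of completed video sessions is documented in the same paragraph, exists for every child in the intervention group and drops when attendance drops. Diary entries made before stopping also remain. This stands, and it limits the point to the diary.

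Two stronger readings are tempting. A reader might infer that exercise compliance is recorded only at sessions the child attends, so that a child who stops has no score. The documents do not support this. The session record contradicts it, the diary interval may refer to scheduled sessions, and a web form can be filled in without attending. Nor does any sentence say that the session percentage is left out of the compliance outcome. A reader might also infer that the group comparison is biased toward the intervention. Exercise compliance is recorded in one arm only, so no between-group test on it is affected. The airway clearance diary is kept in both arms, but by different routes, and the article does not show which arm would have more gaps. The direction of any bias in the difference is therefore unknown.

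It can also be said that the imputation model belongs in a fuller document and could condition on attendance and earlier entries. That is fair as to the model, and such conditioning would reduce the bias. It does not dispose of the point: the article states a rule covering every remaining missing value, and for diary gaps caused by stopping, that rule is ill-suited as worded.

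Finally, the Abstract calls adherence to airway clearance a secondary objective, and the stated compliance hypothesis concerns airway clearance, not exercise. This lowers the weight of the exercise part, although Table 1 still lists both under primary outcomes.

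**Conclusion.** The concern holds for the diary-based compliance measures. The stated rule imputes their gaps as it would any other missing value, and where a gap arises from stopping, this would tend to overstate adherence. For exercise the consequence is an inflated description of one arm. Under the stated assumptions, with 2 of 16 children stopping partway, the inflation is 2.5 to 7.5 points; with 1 to 4 stopping it ranges from 1.25 to 15 points. It is smaller if children continue some exercise after stopping or if imputation uses attendance. The percentage of completed video sessions is unaffected. The change is worth making because the outcome is listed as primary and a suitable record is already kept.

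**What to change.** In 2.8.1 and 2.10:

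- Exclude exercise compliance from multiple imputation.
- Name the documented percentage of completed synchronous sessions, out of 24 scheduled and with missed sessions counted as not done, as the exercise-compliance measure.
- Report diary-based asynchronous exercise separately with two bounds: empty periods counted as not done, and observed periods only.
- For the airway clearance diary, handle gaps identically in both arms and add the same two bounds as a sensitivity analysis. Do not base a scoring rule on leaving the program, since that has no equivalent under usual care and would treat the arms unequally.
- Keep multiple imputation for the modified shuttle walk test and the other measured outcomes.

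The cost is about a paragraph of text. No new data are needed, because session completion and the diaries are already planned. Reported compliance may be lower, and the lower bound will score some activity that was done but not reported as not done.

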#### 2.8.2. Secondary Outcomes

##### Functional and Exercise Capacity

The 6-minute walking test (6MWT) will be used to assess functional capacity. The participants will be asked to walk as far as possible in a 30 m corridor, and standardized encouragement will be given after each minute [29]. The total walking distance (6MWD) will be recorded, and predicted values will be used based on Ulrich et al.’s study [30].

Apart from the MSWT, maximal exercise capacity will be assessed with the Chester step test (CST). The CST is a multi-staged test that requires participants to step on and off a 20 or 25 cm tall step with no handles at a rate set by a metronome beat, which is continuously increasing [31]. Due to the range of ages (6 to 12 years old), these step heights were chosen to be optimal for children according to their age [32]. It consists of 5 levels, each of a two-minute duration. The total number of steps and the maximal level achieved will be recorded. Before, during, and after (recovery period) all tests, cardiorespiratory parameters will be recorded.

Both the 6MWT and CST will be performed twice, with at least 30 min rest. To avoid fatigue, 6MWT will be performed prior to the maximal exercise tests.

##### Health-Related Quality of Life (HRQoL)

Pediatric Quality of Life Inventory Version 4.0 (PedsQL) is a self-administered questionnaire that includes 23 items divided into four subscales: Physical Functioning (PH), Emotional Functioning (EM), Social Functioning (SOC), and School Functioning (SCH) [33]. Responses are given on a five-point scale ranging from 0 (never a problem) to 4 (almost always a problem) and are reverse-scored so that lower scores reflect more negative functioning.

#### 2.8.3. Exploratory Outcomes

##### Respiratory and Peripheral Muscle Strength

Maximal inspiratory (MIP) and expiratory (MEP) pressure will be measured using a mouth pressure meter (MicroRPM; MicroMedical, Lewiston, ME, USA) to assess respiratory muscle strength [34]. A maximum value of three efforts with a variation of less than 5% will be recorded for both inspiratory and expiratory pressures. There will be a minute of rest between the efforts.

Handgrip strength will be assessed using a hand dynamometer (JAMAR, Patterson Medical, Warrenville, IL, USA). Participants will hold the dynamometer at a 90° angle to their elbow. Three separate efforts for the dominant hand grip (DHG) and three for the non-dominant hand grip (NDHG) will be administered, with 30 s of rest between efforts. The highest value in kilograms (kg) for each hand will be recorded [35,36].

##### Physical Activity and Sedentary Behavior

The Physical Activity Questionnaire for Older Children (PAQ-C) is a ten-item self-administered questionnaire that intends to measure PA [37]. Nine of the ten items are scored on a five-point rating scale, where higher scores indicate a higher level of activity. The first item of the PAQ-C consists of 22 common sports and leisure activities for which the participants select the score based on the frequency of the activities performed during the preceding seven days on a five-point rating scale (1 = no activity at all, 2 = 1–2 times, 3 = 3–4 times, 4 = 5–6 times, and 5 = 7 times or more) after a mean composite score is calculated. The remaining eight items address PA performed during the day (e.g., physical education classes, recess time, lunchtime, and after-school activities on weekday evenings and weekends) and a summary for all days of the week. The mean score of the first nine items is the summary score of the PAQ-C.

The Youth Activity Profile (YAP) comprises 15 items in total, each scored on a 5-point scale designed to capture four components in youth behaviors: (1) PA in school, (2) PA out of school, (3) PA over the weekend, and (4) sedentary behaviors [38]. Each YAP section is developed to be scored independently (i.e., items for each dimension score would reflect a higher expected activity level/sedentary time in that same dimension).

##### Cough-Specific Quality of Life (CC-QoL)

The Cough-specific Quality of Life (CC-QoL) is a 7-day recall questionnaire designed to reflect several domains related to a child’s cough, including physical (e.g., coughing makes you feel tired), social (e.g., others staring at you), and psychological (e.g., feeling upset) factors [39]. The responses are rated on a 7-point Likert scale (1 = all the time to 7 = none of the time), with higher scores reflecting higher QoL.

##### Digital Health Services Satisfaction

Satisfaction from the use of the VSee platform and FysAΩ website (www.fysao.gr) will be assessed using the Telemedicine Usability Questionnaire (TUQ). The TUQ consists of 21 questions, scored on a Likert scale from 1 (totally disagree) to 7 (totally agree) [40]. The total score is calculated by the mean of all 21 questions [41].

### 2.9. Sample Size Calculation

Due to the lack of pilot data for this specific population, the effect size was estimated a priori. We targeted a moderate effect size (f = 0.25), assuming that this represents a clinically significant improvement in exercise capacity for children with CSLDs. The required sample size was calculated with G*Power version 3.1.9.4 (G*Power, University of Düsseldorf, Düsseldorf, Germany). The “F-test” (ANOVA: repeated measures, within-between interaction) and the detection of a moderate effect size f = 0.25 (alpha level = 0.05, power = 80%) showed that a total of twenty-eight children are required. Assuming a dropout rate of 10%, the total sample size is estimated at thirty-two children, with sixteen in each group.

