### 2.8. Outcome Measurement

#### 2.8.1. Primary Outcome

##### Exercise Capacity (Modified Shuttle Walk Test)

Maximal exercise capacity will be assessed through the modified shuttle walk test (MSWT). Its reliability has been previously evaluated in the pediatric population with CF [9]. In pediatric populations with CF, a 60 m improvement in the MSWT following a 6-week home-based exercise program has been identified as the minimal clinically important difference [25]. During the MSWT, participants will be asked to walk rapidly at gradually increasing speeds (15 levels total) along a 10 m corridor [26,27]. An audio signal (“beep”) will mark the transitions between levels, signaling a required increase in velocity. The protocol will commence at a baseline speed of 0.5 m/s (Level 1), with an incremental increase of 0.17 m/s for each subsequent level. The test will be terminated based on inability to continue, symptomatic fatigue, or the failure to reach the course marker before the auditory signal on two consecutive occasions. The walking distance (MSWD) will be recorded, and performance will be compared based on the equation proposed by Pinho et al. [28]. Two trials will be performed, with at least a 30 min rest. Before, during, and after (recovery period), cardiorespiratory parameters will be continuously recorded.

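### Section 2.9 calls its target effect moderate, but the f = 0.25 that yields 28 children is a large effect on the scale in Section 2.10 (about 1.06 SD), and it is not linked to the 60 m figure cited for the same test

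*Protocol article*

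**What the plan says.** Section 2.9 (Sample Size Calculation) explains that pilot data are lacking and then sets the effect by convention: "We targeted a moderate effect size (f = 0.25), assuming that this represents a clinically significant improvement in exercise capacity". The procedure is the G*Power module "ANOVA: repeated measures, within-between interaction" with "alpha level = 0.05, power = 80"%. It "showed that a total of twenty-eight children are required". The section continues: "Assuming a dropout rate of 10%, the total sample size is estimated at thirty-two children, with sixteen in each group". It gives no difference in metres, no SD and no within-child correlation.

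Section 2.8.1, on the modified shuttle walk test (MSWT), reports that in children with cystic fibrosis (CF) "a 60 m improvement in the MSWT following a 6-week home-based exercise program has been identified as the minimal clinically important difference". Section 2.9 does not refer to it.

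Section 2.10 (Statistical Analysis) plans a 2 × 3 mixed ANOVA and grades the group × time interaction by partial eta-squared: 0.01 to 0.059 is small, 0.06 to 0.139 is medium, and "a value >0.14 represents a large effect".

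**The concern.** Sections 2.9 and 2.10 concern the same interaction test, yet their effect-size labels are on different scales. With the default effect-size option, G*Power defines f relative to the SD at one time point and brings the correlation in separately, through the noncentrality. That f is not the f = 0.25 that corresponds to a partial eta-squared of about 0.059. A reader who takes moderate in Section 2.9 to mean what medium means in Section 2.10 will believe the trial has 80% power for an effect much smaller than the one it was sized for.

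The statement that f = 0.25 is clinically significant has no support in the article, although a figure in metres for this primary outcome is quoted one section earlier. What is at stake is the claimed power of the trial, and with it what a non-significant result can be said to exclude.

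**Working it through.** **Inputs.** From Section 2.9: f = 0.25, alpha 0.05, power 80%, dropout 10%. From Section 2.10: k = 2 groups, m = 3 time points. Assumed, because not stated: correlation ρ = 0.5 and sphericity ε = 1 (the software defaults).

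**1. Reproducing the plan's figure.** Noncentrality λ = f²·N·m/(1 − ρ), with df1 = (k − 1)(m − 1) = 2 and df2 = (N − k)(m − 1).
- N = 28: λ = 0.0625 × 28 × 3 / 0.5 = 10.5 on 2 and 52 df; power 0.812.
- N = 26: λ = 9.75; power 0.778.
- So 28 is the smallest even N. Dropout: 28/0.9 = 31.1, which becomes 32 with equal arms.
- Other settings do not give 28: two time points give 34; ρ = 0.3, 0.6 and 0.7 give 38, 24 and 18; the effect-size options on the partial eta-squared scale give 80 or 82.

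**2. The same effect on the Section 2.10 scale.** Partial eta-squared = λ/(λ + df2) = 10.5/62.5 = 0.168. With N in place of N − k it is 10.5/(10.5 + 56) = 0.158. Both exceed 0.14.

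**3. The same effect as a group difference.** In units of the single-visit SD, f² is the mean over visits of (d_t − d̄)²/4, where d_t is the group difference at visit t and d̄ is its mean.
- Equal at baseline, difference d at 12 weeks, fully kept (0, d, d) or fully lost (0, d, 0): f = d/√18, so d = 0.25 × 4.243 = 1.06 SD.
- Half lost by follow-up (0, d, d/2): f = d/√24, so d = 0.25 × 4.899 = 1.22 SD.
- Simulation with 14 per arm, ρ = 0.5 and differences of 0, 1.06 and 1.06 SD gave 81.4% power.

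**4. Power for a medium effect as Section 2.10 defines it.** For partial eta-squared η², λ = 52·η²/(1 − η²). No correlation is needed, because η² already contains it.

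| Partial eta-squared | λ | Power, 28 children |
|---|---|---|
| 0.06 | 3.32 | 33% |
| 0.139 | 8.39 | 71% |
| 0.168 | 10.5 | 81% |

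Using 56 (from N) in place of 52 gives 36% and 75% for the two ends of the medium band, still below 80%. If f = 0.25 is meant on this scale (0.0625/1.0625 = 0.059), 80 to 82 evaluable children are needed, depending on the convention.

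**5. What 60 m would mean.** 60 m equals 1.06 SD only if the MSWT SD is 60/1.061 ≈ 57 m. The article gives no SD, so the SDs below are assumptions (28 evaluable children, pattern 0, d, d).

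| Assumed SD | 1.06 SD in metres | Power for 60 m, ρ = 0.5 | Power for 60 m, ρ = 0.8 |
|---|---|---|---|
| 75 m | 80 | 56% | 93% |
| 100 m | 106 | 34% | 71% |
| 150 m | 159 | 17% | 37% |
| 200 m | 212 | 11% | 22% |

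**The case against.** The strongest reply is that Section 2.9 contains no arithmetic error: 28 and 32 both reproduce. It is also candid, since it says that pilot data are lacking and introduces clinical significance as an assumption. An f of 0.25 is conventionally called moderate as an f value. All of that stands. It answers a charge of miscalculation, not the conflict with Section 2.10, which grades the same interaction on another scale.

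A second reply is that the true correlation may exceed 0.5, so that smaller differences become detectable: about 0.81 SD at 0.7 and 0.66 SD at 0.8. This is correct, and 1.06 SD should not be read as a fixed limit of 28 children. It does not rescue the label. At ρ = 0.7 the same f has λ = 17.5 and a partial eta-squared of 17.5/69.5 = 0.25, which is further into the large range. At ρ = 0.3 it is 7.5/59.5 = 0.126, which is medium, but power is then only 66%.

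A reader might go further and infer that a true 60 m effect would probably be missed. The documents do not support that. Over the assumed SDs and correlations above, power for 60 m runs from about 11% to 93%. The 60 m figure is also described as an improvement after a 6-week programme in CF. This trial excludes CF, runs for 12 weeks and compares groups, and nowhere adopts 60 m as its between-group target. Nor do the documents say that a null result would be read as excluding clinical benefit. A rule to judge the confidence interval against 60 m would be a reporting preference, not a correction.

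**Conclusion.** The sample size stands; the account of what it can detect does not. Under the inputs that produce 28, the trial has about 81% power for a partial eta-squared of 0.16 to 0.17, or about 1.06 SD, rising to 1.22 SD if half the effect fades by follow-up. Section 2.10 calls that large. Across its medium band the power is about 33% to 71%, so 80% power for a moderate effect, as Section 2.10 grades effects, is not a property of this design.

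The SD conversion assumes equal baselines and the stated effect patterns, but no particular correlation. The reproduction of 28 rests on the assumed defaults of 0.5 and sphericity. The clinical-significance statement is unsupported, and the power for 60 m is undetermined rather than shown to be low. This should be fixed, but it does not call for a different design.

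**What to change.** Keep 32 children and reword Section 2.9:

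- State which G*Power effect-size option was used, and the inputs: three time points, and the correlation and sphericity values entered (0.5 and 1 if the defaults were used).
- Replace moderate with large, giving the meaning: about 1.06 SD between groups, partial eta-squared about 0.16.
- Either remove the assumption that f = 0.25 is clinically significant, or express the target in metres over a stated range of MSWT SDs and correlations.
- If 60 m is mentioned there, say that it comes from CF and describes improvement after a programme, so that using it as a between-group target is itself an assumption.

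The cost is the rewording of one section, with no extra children and no change of analysis. The downside is that the stated power claim becomes less favourable.
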